#### Quality assurance and control procedures

2.6.4

To ensure data quality, the following measures will be implemented: (1) All data collectors will receive standardized training and certification. (2) Measurement equipment will be calibrated regularly. (3) Key anthropometric measurements (height, weight, waist circumference) will be taken in duplicate by independent staff; a third measurement will be taken if the difference exceeds pre-set tolerances, with the median value recorded. (4) Strict Standard Operating Procedures (SOPs) will be followed for the collection, processing, and storage of all biological samples. (5) Data will be entered electronically using a double-entry system with validation checks to ensure accuracy.

### Implementation evaluation

2.7

Implementation of fidelity and exposure will be assessed to validate intervention effects. Metrics will include:

(1) School-level compliance with the meal plan (e.g., provision of ≥50 g of coarse cereals per student per day).(2) Participant attrition rates at T1 and T2.(3) Comparison of overweight/obesity outcomes between compliant and non-compliant schools.(4) Individual-level adherence, which will be assessed based on the 3-day 24-h dietary recall data collected at T1. High adherence is defined as an estimated average daily coarse-cereal intake of ≥40 g, while low adherence is defined as an intake of <25 g.(5) A prespecified subgroup analysis comparing outcomes between participants with high adherence and those with low adherence.

Paired *t*-tests and standardized regression coefficients will be used to evaluate outcome changes and the impact of confounding factors. Analyses will adjust for confounding factors (e.g., age, sex, baseline BMI). The impact intensity of each variable will be determined using standardized regression coefficients.

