### Randomization and allocation

2.2

Clusters, defined as individual schools, serve as the unit of randomization. The study population is drawn from public primary schools in Huairou District, Beijing, where the prevalence of overweight and obesity among school-aged children exceeds 30%, highlighting the need for effective interventions.

Eligible schools met the following criteria: (1) Availability of an on-site cafeteria capable of providing daily breakfast and lunch to ensure consistent implementation of coarse-cereal substitution; (2) No dietary intervention programs implemented in the past year; (3) Enrollment of at least 150 students in grades 3–4 (ages 8–12) to ensure sufficient sample size per cluster, and (4) Approval from school administrators to participate in the trial.

Two schools meeting these criteria will be randomly assigned to either the intervention or control group using a computer-generated random number table (SAS 9.4).

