##### Coarse-cereal substitution

2.4.2.1

According to the Dietary Guidelines for Chinese Residents (22), children aged 7 ~ 13 years should consume 30–70 g of coarse cereals or legumes daily. In the intervention school, approximately 50 g of coarse cereals per student per day will be provided through the substitution of refined grains in school meals. This target amount is within the recommended range and will be integrated into breakfast, lunch, and dinner (the latter for boarding students only).

To ensure dietary diversity and palatability, the research team, in collaboration with school kitchen staff, developed a standardized coarse-cereal menu. The intervention will utilize common types of coarse cereals and legumes such as oats, brown rice, buckwheat, millet, corn grits, red beans, and mung beans. Over 100 dishes across 12 categories (e.g., buckwheat noodles, red bean rice, millet congee, oat steamed bread) were created, with menus designed to rotate weekly. The core substitution method is a direct, gram-for-gram replacement: coarse cereals will constitute a portion of the staple food, for instance, by using brown rice to partially or wholly replace white rice, or by incorporating whole wheat/oat flour into wheat flour for making buns and noodles. Each daily menu is designed to provide approximately 50 g of coarse cereals and about 4 g of dietary fiber per student, based on calculations from the China Food Composition Tables.

A registered dietitian will audit the school meal menus every 2–3 days to verify coarse-cereal types, portion sizes, and rotation frequency. Coarse cereals will be prepared by steaming, boiling, or stewing to minimize nutrient loss. Recipes were adjusted after pilot testing to balance nutrient content and student acceptance to optimize compliance.

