### Limitations

3.4

Several limitations should be considered within the context of this pragmatic design. First, the 3-month intervention period may not capture long-term effects, although the 6-month follow-up provides a partial evaluation of maintenance. Second, as a pilot pragmatic cluster-randomized trial (pRCT) conducted in only two primary schools in suburban Beijing, the findings are primarily applicable to similar settings with on-site cafeterias. While the limited number of clusters may increase the risk of baseline imbalance, this pilot scale was necessary to test the feasibility and implementation fidelity of the intervention before wider rollout. Third, consistent with the nature of pragmatic trials conducted in real-world settings, blinding of participants and school staff was not feasible. Although this introduces the potential for performance bias, it reflects the actual conditions under which such dietary interventions would be implemented. To mitigate detection bias, we strictly maintained blinding of outcome assessors for anthropometric and biological measurements. Finally, unmeasured confounders, such as family lifestyle factors not captured in current assessments, may influence outcomes, a challenge common to school-based community interventions.

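### The planned outcome comparison of compliant with non-compliant schools cannot be made separately from the arm contrast, because only one school has a coarse-cereal meal plan

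*Protocol article*

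**What the plan says.** Section 2.2 (Randomization and allocation) sets the design: "Clusters, defined as individual schools, serve as the unit of randomization", and "Two schools meeting these criteria will be randomly assigned to either the intervention or control group". Section 3.4 (Limitations) confirms the number, describing a pilot "conducted in only two primary schools in suburban Beijing".

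Section 2.4.2.1 (Coarse-cereal substitution) assigns the meal plan to a single school: "In the intervention school, approximately 50 g of coarse cereals per student per day will be provided". Section 2.4.4 (Control group) keeps the control arm on its standard meals, with no substitution.

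Section 2.7 (Implementation evaluation) presents its five metrics as a way of validating the intervention effect. Item (1) is school-level compliance with the meal plan, illustrated by "provision of ≥50 g of coarse cereals per student per day". Item (3) is a "Comparison of overweight/obesity outcomes between compliant and non-compliant schools". Items (4) and (5) concern individual adherence and are a separate matter.

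**The concern.** Item (3) needs at least one school in each compliance group, and compliance is defined against a meal plan that only one school has. The only way to fill both groups is to classify the control school as well. The result is then the randomised comparison under a second name, in a section whose stated purpose is to validate the effect. A reader of the results could take one between-school difference, reported twice, for two pieces of evidence. This matters because section 3.4 justifies the two-school scale by the need to test feasibility and implementation fidelity, so fidelity reporting is one of the reasons for running the pilot.

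A smaller question is whether the example cut in item (1) fits the menu specification, since one is a floor and the other an approximate target at the same value.

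**Working it through.** The plan gives no figure to reproduce here. The check is structural.

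**Inputs**
- Schools randomised: 2, one per arm (sections 2.2 and 3.4).
- Schools with a coarse-cereal meal plan: 1, the intervention school (sections 2.4.2.1 and 2.4.4).
- Planned comparison: compliant against non-compliant schools (section 2.7, item 3).

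**Step 1: classify only schools that have a meal plan.** There are 2 − 1 = 1 such schools. If it complies, the non-compliant group has 0 schools. If it does not, the compliant group has 0 schools. No comparison exists in either case.

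**Step 2: classify both schools.** There are 2 × 2 = 4 labellings.

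| Intervention school | Control school | What item (3) becomes |
|---|---|---|
| compliant | compliant | non-compliant group empty |
| non-compliant | non-compliant | compliant group empty |
| compliant | non-compliant | the arm contrast |
| non-compliant | compliant | the arm contrast with labels reversed; implausible, as the control school has no substitution |

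No row gives information on compliance that is distinct from arm.

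**Step 3: degrees of freedom.** Two schools with two group means leave 2 − 2 = 0 degrees of freedom for between-school error. The two schools supply one between-school difference, and the arm comparison already uses it.

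**Step 4: does the cut matter?** Steps 1 to 3 use no threshold. Changing the cut can change the label a school receives, but it cannot create a second school on the meal plan.

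**Step 5: the cut against the menu.** Section 2.4.2.1 states: "Each daily menu is designed to provide approximately 50 g of coarse cereals". Section 2.7 gives as its example "provision of ≥50 g of coarse cereals per student per day". A menu built to an approximate target may deliver slightly under or slightly over it. A floor at the same value can therefore label a school non-compliant although it is working to plan. The documents give neither the mean nor the spread of the amount served, so how often this would happen cannot be calculated.

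**The case against.** The case on the other side has five parts.

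- **Item (3) is one line among five process metrics.** The primary test in section 2.6.2 does not use it, and adherence is also examined at individual level (section 2.7, items 4 and 5; per-protocol analysis in section 2.6.3). This stands, and it limits the severity.
- **The cut is only an example, and its operational definition may sit in the full protocol.** This also stands. A reader might infer that a kitchen working to plan would fail on about half of its days. The documents do not support that. Section 2.7 sets no day-by-day pass or fail rule, and grams per student per day can be read as an average over the period. Exactly 50 g meets a floor of 50 g, and no spread is given.
- **The harm is conjectural.** A reader might infer that item (3) would be presented as dose-response evidence, or that a null result would be blamed on poor delivery. Nothing in the article says either. The validation purpose introduces all five metrics and is not claimed for item (3) alone.
- **An article condenses a fuller plan.** This does not rescue item (3). The objection is not to missing detail but to a stated analysis that the stated design cannot support. More detail would help only by changing the number of schools or the unit of comparison.
- **Section 2.4.4 refers to control schools in the plural.** Sections 2.2 and 3.4 fix the total at two, and a further control school would still have no meal plan to comply with.

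**Conclusion.** The point holds in limited form. Item (3) of section 2.7 cannot be carried out as a comparison of compliance. It has 0 schools in one group, or it is the arm contrast relabelled, with 0 between-school degrees of freedom. It therefore cannot validate the intervention effect. This rests only on the stated count of two schools and on the meal plan being given to one of them; no numerical assumption is needed.

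The mismatch between the approximate 50 g target and the example floor of 50 g is a separate wording point. It plays no part in the emptiness of the comparison and has no quantifiable size from the documents.

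Severity is minor. Item (3) enters neither the primary analysis nor the sample size, so removing it changes neither. A reader might go further and take this as a fault in the primary model or in the individual-adherence analyses. It is neither: those do not use item (3), and items (4) and (5) are not empty for this reason.

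**What to change.** Delete item (3) from section 2.7. In its place, report delivery within the intervention school descriptively: grams of coarse cereals served per student over the intervention period, and the percentage of the planned amount. The sources are already planned, namely the canteen staff's daily menu records (section 2.5.1.1) and the dietitian's audits every 2–3 days (section 2.4.2.1). Add a sentence saying that these data describe delivery and do not validate the effect.

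Reconcile the menu target in section 2.4.2.1 with the example compliance cut in section 2.7, so that delivery to plan is not labelled non-compliant. Which value or tolerance to use is for the investigators to decide.

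The cost is a change of protocol wording. No new data are needed, and the only thing given up is an analysis that could not be run as named.

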##### 3-Day 24-hour dietary recall (3D-24HR)

2.5.1.1

Students recorded all food and beverage intake over three consecutive days (two weekdays, one weekend) at T0, T1, and T2. Kitchen scales will be provided to measure portions, and cooking methods will be recorded. Canteen staff documented daily menus to calculate in-school coarse-cereal intake. Parents maintained weekly coarse-cereal purchase and cooking logs. Daily intake (g/day) will be calculated using the China Food Composition Tables.

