#### Subgroup and sensitivity analyses

2.6.3

Pre-specified subgroups included se and baseline BMI category. Three way interactions (group x time x subgroup) tested effect modification, with Bonferroni correction (*α* = 0.025). Per-protocol analysis excluded participants with <50% intervention adherence. Complete-case analysis will be conducted to assess robustness to missing data.

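### Adherence is averaged over a weekend day although the cereal comes in school meals, so many children who eat the full school amount fall in an unclassified band

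*Protocol article*

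**What the plan says.** Four parts of the protocol article bear on this point.

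- **Delivery (section 2.4.2.1).** "approximately 50 g of coarse cereals per student per day will be provided through the substitution of refined grains in school meals". No weekend meal provision is described.
- **Measurement (section 2.5.1.1).** Intake is recorded over "three consecutive days (two weekdays, one weekend) at T0, T1, and T2".
- **Adherence classes (section 2.7).** "Individual-level adherence, which will be assessed based on the 3-day 24-h dietary recall data collected at T1". Then: "High adherence is defined as an estimated average daily coarse-cereal intake of ≥40 g", while "low adherence is defined as an intake of <25 g". A prespecified analysis compares the high class with the low class. Intakes from 25 g to under 40 g belong to neither.
- **Per-protocol rule (section 2.6.3).** "Per-protocol analysis excluded participants with <50% intervention adherence". The rule names no arm and does not say which measure of adherence it uses.

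**The concern.** The cut-offs look like fractions of the daily school amount: 40/50 = 80% and 25/50 = 50%. They are applied, however, to an average in which one day in three is not a school day. Section 2.5.4 separates school days from weekend days in the same way when it describes wristband wear.

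A child can therefore eat everything the school serves and still not be classed as highly adherent. Whether that child crosses 40 g depends on what the family serves at home, and section 3.4 itself names family lifestyle as a possible source of unmeasured confounding.

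Three things are at stake. Full compliers may vanish from the high-versus-low comparison. That comparison may partly reflect home diet rather than uptake of the school meals. And good delivery may be recorded as less than high adherence in a section whose stated purpose is to support the intervention effect.

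**Working it through.** The cut-offs are stated rather than derived, so there is no calculation in the plan to reproduce. The check asks what a child must eat to be placed in each class.

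**Inputs**
- School amount eaten per weekday: *s* = 50 g for a full complier (section 2.4.2.1).
- Recall days: two weekdays and one weekend day (section 2.5.1.1).
- Cut-offs: 40 g and 25 g (section 2.7).
- Coarse cereal eaten outside school: *h* g per weekday and *w* g on the weekend day. The plan gives no value for either. Its only background figure is a national mean of 8 g/day in 2020 (section 3.1). I therefore vary *h* and *w*. The value 2.7 g is an assumed one third of 8 g eaten at home on a weekday.
- Assumption: no school meals on the weekend day.

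**Formula.** Three-day mean = [2(*s* + *h*) + *w*] / 3.

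**Full complier, *s* = 50 g**

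| *h* (g) | *w* (g) | Three-day mean | Class |
|---|---|---|---|
| 0 | 0 | 100/3 = 33.3 g | none |
| 0 | 8 | 108/3 = 36.0 g | none |
| 2.7 | 8 | 113.3/3 = 37.8 g | none |
| 0 | 20 | 120/3 = 40.0 g | high |
| 8 | 8 | 124/3 = 41.3 g | high |

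A mean of 40 g needs a three-day total of 120 g. School supplies 100 g, so 2*h* + *w* must be at least 20 g.

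The shortfall is not only a matter of sampling one weekend day in three. With a true 5:2 week and *h* = 0, the mean is 250/7 = 35.7 g with nothing at weekends and (250 + 16)/7 = 38.0 g with 8 g on each weekend day.

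**Low cut-off.** Avoiding the low class needs a three-day total of 75 g, so *s* must be at least (75 − 2*h* − *w*)/2:
- *h* = *w* = 0: 37.5 g per school day, 75% of 50 g.
- *h* = 0, *w* = 8: 33.5 g, 67%.
- *h* = *w* = 8: 25.5 g, 51%.

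The 25 g cut thus corresponds to about half the school amount only if the child also eats about 8 g outside school every day.

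**Scored on weekdays only.** With *h* = 0 the full complier averages (50 + 50)/2 = 50 g and is clearly high.

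**The case against.** The strongest reply is that home intake belongs to the intervention. Section 2.4.3.2 teaches parents to cook coarse cereals at home, so a measure of total intake that includes a weekend day is defensible, and dropping that day altogether would ignore the parent component. This stands, and it is why the fix keeps home intake as a separate measure. It does not rescue the 40 g cut: no gram target for home intake is given, and a single average cannot separate uptake at school from uptake at home.

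The result is also sensitive to weekday home intake. With 8 g outside school every day, the full complier reaches 41.3 g. That is a fair limit on the claim. But 8 g is a whole-day mean, and breakfast and lunch are school meals here, so the full amount on top of them is a favourable assumption.

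Leaving out a middle band to compare extremes is common practice, and the child at 33 to 38 g is not labelled low. That stands too. The difficulty is that this band holds children who took everything the school offered.

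Some stronger readings are tempting and are not supported:
- A reader might infer that no full complier can be classed high. The table shows otherwise.
- Section 2.7 gives "provision of ≥50 g of coarse cereals per student per day" as an example of school compliance, while section 2.4.2.1 says "Each daily menu is designed to provide approximately 50 g of coarse cereals". A reader might infer that about half of menu days would fail. The plan gives no distribution of daily menu amounts and no day-by-day pass rule, so that does not follow.
- A reader might infer that the per-protocol rule would remove nearly all controls, whose intake may lie near 8 g. That requires tying the rule to the 25 g cut and applying it to children who have no intervention to adhere to (section 2.4.4). Section 2.6.3 does neither. Use in the intervention arm only is the natural reading, but it is an inference.
- The aim of supporting the intervention effect is stated for the section 2.7 metrics, not for the per-protocol analysis.

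**Conclusion.** The point holds for the individual adherence classes. On the plan's own rules, eating the full school amount gives a three-day mean of 33.3 to 37.8 g in the first three scenarios of the table. All three lie below the 40 g cut and in the band with no class. Crossing the cut needs at least 20 g of non-school coarse cereal over the three days. Many full compliers would be lost from the high-versus-low comparison, and the high class would partly select on home diet. How many cannot be computed, because the plan gives no distribution of home intake.

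The conclusion rests on there being no school meals at the weekend and on modest home intake on weekdays; it weakens as home intake approaches 8 g every day.

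The per-protocol rule adds a smaller point. It is not linked to the section 2.7 classes, and if it is applied to the intervention arm it compares children selected after randomisation with unselected controls.

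These are secondary and sensitivity analyses. The primary intention-to-treat model in section 2.6.2 is unaffected. The change should be made, but the main result does not depend on it.

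**What to change.** - Score adherence to the school-meal component from the two weekday recalls, as a percentage of the amount provided. The canteen menu records supply the amount provided; they do not show what an individual child ate.
- Report weekend and home intake separately, as uptake of the parent component.
- Use contiguous adherence categories with no gap.
- Reconcile sections 2.4.2.1, 2.5.1.1, 2.6.3 and 2.7: say which days count, tie the 50% per-protocol rule to the same measure, and state that it applies to the intervention arm.
- Label the high-versus-low and per-protocol contrasts as non-randomised, exploratory analyses that cannot validate the intervention effect.

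An instrumental-variable (complier-average) estimate is not a suitable replacement. The education sessions also address snacks, beverages and balanced diet, so allocation can act by routes other than cereal intake. With one school per arm, allocation also cannot be separated from school.

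The cost is small, because the recalls and menu records are already planned. The downside is that each child's adherence rests on two recall days instead of three and will be less precise.

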#### Sample size calculation

2.3.1

The primary outcome for sample size estimation was the Body Mass Index Standard Deviation Score (BMI-SDS). Due to the lack of previous studies on coarse-cereal interventions in this population, sample size was estimated based on prior research evaluating comprehensive interventions on obesity in primary school students. The calculations assumed 80% power (*β* = 0.20), a two-sided significance level of 0.05 (*α* = 0.05), standard deviation *σ* = 1.39, and effect size *Δ* 0.17. The resulting sample size was 180 students per school. Allowing for 10–20% attrition, the target enrollment per school was set at 190–200 students (18). The calculation formula used will be:

$$n=\frac{{\left(Z_{\alpha /2}+Z_{\beta }\right)}^{2}{\left(2\sigma^{2}\right)}^{2}[1+(m-1)\rho ]}{{\left(\mu_{1}-\mu_{2}\right)}^{2}}$$

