### Statistical analysis

2.6

Analysis accounts for the cluster-randomization design, with schools as clusters and students nested within schools. Intention-to-treat (ITT) principles are applied, using SAS 9.4.

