### Rationale and significance

3.1

Coarse cereals, including millet, naked oats, and buckwheat, have a long history in the Chinese diet (6). Despite dietary guidelines recommending 30–70 g of coarse cereals per day for children aged 7–13 years (22), average intake among Chinese children was 8 g/day in 2020. Concurrently, school meal programs in China are being standardized and widely implemented, providing a feasible platform to improve dietary quality and reach a large proportion of school-aged children (24, 25). By integrating coarse-cereal provision into daily meals, this intervention is culturally acceptable and likely to be supported by parents and schools.

This study protocol outlines a school-based pragmatic randomized controlled trial (pRCT) designed to evaluate the real-world effectiveness of a daily 50 g coarse-cereal substitution in preventing obesity among primary school students (grades 3–4, aged 8–12 years) (19). Unlike explanatory trials conducted under highly controlled conditions, this pRCT leverages existing school infrastructure and routine operational workflows to assess the intervention’s impact within the complex reality of the Chinese educational setting. The intervention combines dietary modification, multi-level nutrition education, and digital monitoring tools, addressing critical gaps in childhood obesity prevention research in China. By adopting a pragmatic design, this study aims to generate robust evidence on the feasibility, scalability, and practical effectiveness of coarse-cereal interventions, thereby directly aligning with national public health priorities and informing future policy implementation.

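### The high- versus low-adherence comparison in section 2.7 groups children by intake reported after randomisation and names no arm, so it cannot validate the intervention effect

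*Protocol article*

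**What the plan says.** Section 2.7 (Implementation evaluation) lists five metrics under the opening statement "Implementation of fidelity and exposure will be assessed to validate intervention effects". Item (4) classifies individual adherence by average daily coarse-cereal intake in the 3-day recall at T1: 40 g or more is high, below 25 g is low. Item (5) is "A prespecified subgroup analysis comparing outcomes between participants with high adherence and those with low adherence". Neither item names an arm. The section plans adjustment for confounders and gives age, sex and baseline BMI as examples. Section 2.5.4 adds physical activity, dietary preference and cognition, and home environment to the variables to be adjusted for.

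For the main analysis, section 2.6 states that "Intention-to-treat (ITT) principles are applied", and section 2.6.2 puts the primary test on the group-by-time interaction. Section 2.6.3 names its subgroups as sex and baseline BMI category, both fixed before randomisation.

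**The concern.** A subgroup analysis compares randomised arms within levels of a baseline characteristic. Item (5) compares children with each other according to what they reported eating three months after allocation. Children who keep eating the cereals may differ from those who do not in appetite, family diet and reporting. Because the cut-offs are in absolute grams, the high group also tends to include children who eat more overall. Such differences can produce a gap in BMI-SDS in either direction when the intervention does nothing.

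At stake is a supporting conclusion. The analysis is prespecified and sits in a section whose stated aim is validation, so a favourable gap could be read as confirming the intervention effect, and an unfavourable one as contradicting it. Neither reading would be warranted.

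**Working it through.** The plan gives no expected result for item (5), so there is no figure to reproduce. The benchmark is the planned effect in section 2.3.1, "effect size *Δ* 0.17", taken as stated.

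**1. What the 40 g cut-off measures in the intervention arm.** Section 2.5.1.1: the recall covers two weekdays and one weekend day. Section 2.4.2.1: school meals supply about 50 g per day. Assume that both weekdays are school days.

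- All school cereals eaten, none elsewhere: (50 + 50 + 0)/3 = 33.3 g/day, below the high cut-off.
- Shortfall: 3 × 40 − 100 = 20 g over the three days.
- Adding 8 g on the weekend day only: 108/3 = 36 g/day, still below.
- Adding 8 g outside school meals on all three days: 124/3 = 41.3 g/day, just above.

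The 8 g is illustrative and comes from section 3.1 ("average intake among Chinese children was 8 g/day in 2020"). A child who complies fully at school is therefore classed as high or not according to food outside the school menu or larger school portions.

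**2. If both arms were pooled on the grams rule.** Assumptions: control intake gamma-distributed with mean 8 g and SD 8 or 12 g; intervention intake normal, floored at zero, with mean 35–45 g and SD 15 g. Simulated results:

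- about 92–96% of control children fall below 25 g;
- control children make up about 78–91% of the low group;
- intervention children make up about 93–99% of the high group.

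**3. Bias within the intervention arm with no true effect.** Let g be the difference in mean intake between the high and low groups, in SDs of intake. Let r be the non-causal correlation between intake and outcome that remains after adjustment, assumed linear, and s the residual SD of the outcome. Then

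spurious difference = r × g × s, so the r needed for 0.17 is 0.17/(g × s).

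Hand check for mean 40 g, SD 15 g. The cut-offs lie at z = 0 and z = −1. Mean z above 0 is 0.3989/0.5 = 0.798; mean z below −1 is −0.2420/0.1587 = −1.525. So g ≈ 2.32, against 2.33 by simulation with intake floored at zero.

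| Assumed mean / SD of intake (g) | g | r needed, s = 0.5 | r needed, s = 0.3 |
|---|---|---|---|
| 30 / 15 | 2.31 | 0.147 | 0.245 |
| 35 / 15 | 2.29 | 0.148 | 0.247 |
| 40 / 15 | 2.33 | 0.146 | 0.244 |
| 45 / 15 | 2.39 | 0.142 | 0.237 |
| 40 / 20 | 2.13 | 0.159 | 0.266 |

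Read the other way, r = 0.1 gives a spurious difference of about 0.11–0.12 at s = 0.5 and 0.06–0.07 at s = 0.3. With r = 0.2 the figures are 0.21–0.24 and 0.13–0.14. The intake distributions, r and s are all assumptions; none is in the documents.

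**The case against.** **Control children are not said to be classified.** A reader might infer that control children count as low adherers to an intervention they were never offered. The documents do not support that. Section 2.5.1 ties adherence to the 3-month intervention and treats control intake as a separate comparison. Section 2.6.3 speaks of intervention adherence below 50%, and 25 g is 50% of the 50 g supplied only in the intervention school. The 8 g figure is a national average, not the control school's intake. This objection stands: the defect is an unstated population. It remains a real ambiguity, because item (3) of the same list compares compliant with non-compliant schools. With one school per arm, that contrast can exist only if one whole arm is classed as non-compliant.

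**Adjustment is planned.** Section 2.5.4 covers snack choices, preference for coarse cereals, availability at home, cooking frequency and role modelling, so family diet and snacking are partly addressed. That reduces the bias but cannot be assumed to remove it. The questionnaire has only face validity, total appetite is not on the list, and section 3.4 concedes unmeasured family lifestyle factors.

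**A trivial correlation is not enough.** With "standard deviation *σ* = 1.39" the required r would be only about 0.05–0.06. That uses the unadjusted SD, whereas section 2.7 adjusts for baseline BMI, so the larger values above are the relevant ones.

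**Noise may dominate.** For mean 35 g and SD 15 g, shares of 37% and 25% of 200 children give about 74 high and 50 low. The standard error is s × √(1/74 + 1/50) = 0.183 × s. That is 0.25 at s = 1.39, so 0.17 would be lost in noise, but 0.09 at s = 0.5 and 0.05 at s = 0.3. On the adjusted scale a spurious 0.17 is about 1.9 or 3.1 standard errors.

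**The validation phrase covers the whole section, and the primary analysis is intention-to-treat.** Both are true and limit the consequence. But item (5) is one of the five metrics under that stated aim, and nothing in the section exempts it.

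**Conclusion.** The point holds as a defect in a supporting analysis that the protocol itself fixes: the cut-offs, the contrast and the purpose are all stated. Item (5) is a non-randomised comparison by post-randomisation intake, its population is not stated, and it cannot validate the intervention effect whichever arm it covers. The primary intention-to-treat analysis is untouched.

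The size is conditional. Confounding alone would reproduce the planned 0.17 BMI-SDS if the residual intake–outcome correlation were about 0.14–0.16 (adjusted SD 0.5) or 0.24–0.27 (adjusted SD 0.3). These are modest but not negligible correlations, they rest on assumed inputs, and the direction is unknown. It does not follow that the bias will be this large, only that the comparison could not distinguish it from a real effect.

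**What to change.** In section 2.7, item (5):

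- restrict the comparison to the intervention arm;
- call it an exploratory, non-causal description of outcome by T1 intake, adjusted for the confounders in section 2.5.4, and drop the word subgroup;
- state that it does not validate the intervention effect, which rests on the intention-to-treat contrast in section 2.6.2;
- note that the three-day average mixes school and non-school days, so the 40 g cut-off does not isolate adherence to school meals.

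It may be tempting to estimate the effect of eating the cereals by using allocated arm as an instrument for intake. That should not be done here. The intervention also teaches students about obesity risk, snacks and beverages (section 2.4.3.1) and gives parents messages and webinars on snacks and weight management (section 2.4.3.2). Arm can therefore affect weight other than through cereal intake, and having one school per arm limits such an estimate further.

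The cost is a few lines of protocol text and no new data. The downside is a less favourable-looking supporting claim.
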